### Secondary Objectives

#### *Duration of Protective efficacy against clinical malaria*

To assess the protective efficacy against clinical malaria of ChAd63 ME-TRAP / MVA ME-TRAP prime-boost immunisation, in 5-17 month old infants and children living in a malaria-endemic area, for 12 and 24\* months after the last vaccination.

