### **Lead-in Safety Evaluation followed by Phase 2b trial**

Confirmation of satisfactory safety of the vaccines in a small sample of the local population of Burkinabe infants and children is desirable before vaccinating the larger number of participants in the Phase 2b trial. Therefore there will be interim assessments of vaccine safety in 30 participants (Group A), with DSMB approvals required to administer vaccines to Group B and C infants. This is detailed in Section 8.

For the Phase 2b trial, participants will be randomised 1:1 to receive vaccination with the IMPs (ChAd63 ME-TRAP and MVA ME-TRAP; Group B) or control vaccination with Rabies Vaccine (Group C). Participants and investigators will be blinded to whether the participant is in Group B or C. Efficacy of vaccination will be assessed by comparing the development of malaria between Group B versus Group C participants.

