## Sample size

For the Lead-in Safety Evaluation, a sample of size of 30 participants has been selected as the minimum number required to provide adequate safety data to enable an interim assessment of safety which could support progressing to the Phase 2b trial.

The primary endpoint of the Phase 2b trial is the time to first episode of malaria meeting the primary case definition of clinical malaria episode, over a period of 6 months. We will aim to time vaccinations so that this 6 month interval (study day 63 to 243) incorporates the malaria season, which runs from June to October.

From the results of a baseline site survey, it is anticipated that during the malaria season, the incidence of malaria meeting the primary case definition of clinical *P. falciparum* malaria episode will be 50% in 5-17 month old infants. Rabies vaccination should not provide any protection against malaria infection. Therefore, the incidence of episodes meeting the primary case definition of clinical *P. falciparum* malaria between Day 63 and Day 243 in Group C should be 50%.

An efficacy of vaccination of 30% is that considered suitable for the vaccine strategy to be included in a future multi-component high efficacy vaccine. With a total sample of 700 participants, the expected power to detect 30% vaccine efficacy, (i.e., a hazard ratio of 0.7, with the proportion of malaria in Group B by Day 243 equalling 38%) will be 88%. Due to the short duration of the study, we anticipate the rate of loss to follow-up or drop out will be minimal. However, even with 20% drop-out or loss to follow-up, the sample size still gives 80% power to detect 30% vaccine efficacy.

| Proportion who develop clinical P. falciparum malaria in Group C | Proportion who develop clinical P. falciparum malaria in Group B | Hazard ratio | Power |
|-------------------------------------------------------------------------|-------------------------------------------------------------------------|--------------|-------|
| 50%                                                                     | 38%                                                                     | 0.7          | 88%   |
| 40%                                                                     | 30%                                                                     | 0.7          | 79%   |

Table 2: Power to assess 30% efficacy of vaccination in the Phase 2b trial

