### ***Primary analysis***

The primary analysis of efficacy will be comparison between Group B and C of the time to first episode of malaria meeting the primary case definition of clinical malaria episode over a period of 6 months of follow up after the last vaccination (ie, from Day 63 to 243). This will be done using survival analysis (e.g. Cox proportional hazard model), adjusting for any stratification factors (age, bednet use). Results will be presented as adjusted hazard ratio with appropriate 95% confidence intervals. Vaccine efficacy will be calculated as 1-HR. Kaplan-Meier methods will be used to visualize the time to first malaria event. The primary analysis will be based on the per-protocol population. An unadjusted analysis will also be carried out on the basis of intention-to-treat.

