#### ***-Protective efficacy against clinical malaria***

- Time to first episode of malaria meeting the primary case definition of clinical malaria episode over a period of 12, and 24\* months of follow-up after the last vaccination.
- Proportion of participants with an episode of malaria meeting the primary case definition of clinical malaria episode, within the periods, 6, 12 and 24\* months of follow-up after the last vaccination (ie, from study day 63 to 243, 63 to 423, and 63 to 738, respectively)

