#### ***-Efficacy against secondary case definitions of clinical malaria episode***

- Time to first episode of malaria meeting the secondary case definitions of clinical malaria episode over a period of 6, 12, and 24\* months of follow-up after the last vaccination.
- Proportion of participants with an episode of malaria meeting the secondary case definitions of clinical malaria, within a period of 6, 12 and 24\* months of follow up after the last vaccination

Time to first or only episode of clinical malaria meeting secondary endpoint definitions will be analysed as above.

Variation in efficacy over time will be examined using Schoenfeld Residuals, and time dependent covariate analysis in Cox Regression. If significant variation in efficacy over time is identified then efficacy will be presented as a summary figure over the full length of follow up, but also as a varying figure over time.

The proportion of children with asymptomatic parasitaemia at the cross-sectional surveys will be presented, and vaccine efficacy evaluated using logistic regression.

Multiple episodes of malaria will be examined using Poisson or negative binomial models on the ATP cohort (negative binomial if the data is over-dispersed) and adjusted incidence rate ratios calculated, adjusted by stratification factors. An unadjusted ITT analysis will also be conducted.

\* Depending on the outcome of the efficacy analysis of the 12 month data, this may be extended to 24 months following completion of vaccination

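### A time-varying efficacy figure is promised only after a significant test; otherwise cumulative estimates stand, and these would often dilute waning

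*Protocol*

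**What the plan says.** Section 4 of the protocol lists "Duration of Protective efficacy against clinical malaria" as the first secondary objective, framed as efficacy for 12 months and, conditionally, 24 months after the last vaccination.

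To answer it, Section 9 plans "Time to first episode of malaria meeting the primary case definition of clinical malaria episode over a period of 12, and 24" months, and the proportion of children affected in windows that all start at Day 63. The 24-month efficacy analysis depends on the 12-month result. No separate window, such as Day 243 to Day 423, is planned for clinical malaria.

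On change over time, Section 9 states: "Variation in efficacy over time will be examined using Schoenfeld Residuals, and time dependent covariate analysis in Cox Regression". It continues with a condition, "If significant variation in efficacy over time is identified": in that case efficacy is given both as one overall figure and as a figure that varies over time. It promises nothing time-specific when the test is not significant.

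The primary analysis text adds that "Kaplan-Meier methods will be used to visualize the time to first malaria event". The only power statement, under Sample size in Section 5, concerns the average effect: "With a total sample of 700 participants, the expected power to detect 30% vaccine efficacy" is 88%. No power is given for a change in the hazard ratio.

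**The concern.** A question about how long protection lasts needs an estimate with a confidence interval for the later period. Here that estimate depends on a significance test. A non-significant test of proportional hazards is weak evidence of constant efficacy when the trial was sized for the average effect and not for a change in it.

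The ungated 12-month figure does not fill the gap, because it reuses the first six months, which are timed to contain the June to October season. Early events therefore dominate it. A VE that has gone to zero can still leave a cumulative 12-month figure close to the 6-month one. The protocol also makes the extension of efficacy analysis to 24 months depend on the outcome of that 12-month analysis.

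**Working it through.** **Inputs from the protocol.** 700 children, and "participants will be randomised 1:1", so 350 per group. First-episode risk from Day 63 to Day 243 is 50% in Group C and 38% in Group B, with hazard ratio (HR) 0.7 (Section 5, Sample size).

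**Assumptions not in the protocol.** Two-sided 5% test; no drop-out; constant hazard within each period; step loss of efficacy at month 6. Control risk in months 6 to 12, among children still without a first episode, is varied from 10% to 50%. The protocol gives no incidence for those months. By the Section 5 timeline they run from about December 2013 to June 2014, largely outside the peak season.

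**The plan's own figure.** Events = 350 × (0.50 + 0.38) = 308. Power = Φ(√(308/4) × |ln 0.7| − 1.96) = Φ(8.775 × 0.3567 − 1.96) = Φ(1.17) = 88%. This agrees with the stated 88% and supports the two-sided 5% assumption.

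**Power to detect loss of efficacy after month 6.** Compare the log HR of months 0-6 with that of months 6-12:

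- SE = √(sum of 1/events over the four group-by-period cells)
- Power = Φ(|ln(HR1/HR2)|/SE − 1.96)

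Worked case, VE 30% then 0%, later control risk 20%:

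- Group C: 350 × 0.50 = 175 early events; 175 × 0.20 = 35 late.
- Group B: 350 × (1 − 0.5^0.7) = 350 × 0.3844 = 134.5 early; 350 × 0.6156 × 0.20 = 43.1 late.
- SE = √(1/175 + 1/134.5 + 1/35 + 1/43.1) = √0.0649 = 0.255.
- Power = Φ(0.3567/0.255 − 1.96) = Φ(−0.56) = 29%.

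**Cumulative 12-month VE in the same case.** Averaging the log HR over events: 309.5 early and 78.1 late, so ln HR = −0.3567 × 309.5/387.6 = −0.285, HR = 0.752, VE about 25%. A large-sample Cox calculation gives 24.7%.

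| Control risk, months 6-12 | Power, VE 30% then 0% | Cumulative 12-month VE (true 30% then 0%) | Power, VE 50% then 0% |
|---|---|---|---|
| 10% | 18% | 27% | 54% |
| 20% | 29% | 25% | 78% |
| 30% | 37% | 23% | 89% |
| 50% | 49% | 20% | 96% |

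**Gradual loss.** The table assumes a step at a known time. In a simulated Cox model with a treatment-by-linear-time term (1,500 runs, size about 5%), VE falling log-linearly from 50% to 0% over 12 months is detected 37% of the time with 20% later risk and 56% with 50% later risk.

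**Precision of the missing estimate.** If the true VE in months 6-12 is 0%, the expected 95% interval is about −56% to 36% with 20% later risk (SE = √(1/35 + 1/43) = 0.228), and about −33% to 25% with 50% later risk.

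**The case against.** A reader might infer that the rule hides waning altogether. The documents do not support that. Cumulative efficacy at 6 and 12 months is reported whatever the test shows, and the duration objective is framed in just those terms. Kaplan-Meier curves are planned for the primary analysis. Asymptomatic infection is assessed at separate cross-sections on Days 243 and 423, and multiple episodes are modelled. The examination of variation is itself unconditional; only the added figure is gated. The text does not say that a non-significant test proves constancy. All of this stands.

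A reader might also call the test weak in general. It is not: a step from VE 50% to 0% is detected 78% of the time or more once later control risk reaches 20%. Power figures from splitting the 6-month window in two do not settle the matter either. They say nothing direct about months 6 to 12, and they range from 24% (HR 0.6 then 0.8) to 97% (HR 0.4 then 1.0) with the pattern chosen.

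The sentence sits under the heading for secondary case definitions, so its scope is open. It reads as general. If it is not, no examination of time variation is promised for the primary definition, which does not help the plan.

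Finally, the choice of intervals commonly belongs in the statistical analysis plan, which Section 9 promises and which is not at hand. That plan may add interval estimates. The point here is the conditional rule that the protocol itself states.

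**Conclusion.** The point holds as a minor improvement to a stated rule. When the test is not significant, the protocol promises only cumulative clinical-malaria estimates from Day 63. For the effect the trial was designed around, that outcome is more likely than not even if protection has gone: complete loss of a 30% VE after month 6 is missed about 51% to 82% of the time (100% minus 49% and 18%). The 12-month figure would then still read about 20% to 27%, or about 25% with 20% later control risk. Stronger waning, VE 50% then 0%, is missed about 4% to 46% of the time. Waning would therefore often be diluted and left without an interval estimate, but not concealed. These sizes rest on the assumed later incidence, the step pattern, a two-sided 5% test and no drop-out. Drop-out or gradual loss would lower the power.

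**What to change.** Whatever the test result, report VE with 95% CI for Day 63-243 and Day 243-423, or a smoothed VE over time, for the primary case definition alongside the overall figure. Add Day 423 to the end of follow-up only if the efficacy analysis is extended to 24 months. Keep the Schoenfeld-residual and time-dependent covariate tests as descriptive support and not as a condition for reporting. State which endpoints the rule covers.

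The cost is a few more rows of output, with no new data, visits or children. There are two drawbacks. Interval estimates are less precise, as the intervals above show. Later-interval hazard ratios for first episodes also compare groups that have been depleted differently: with 50% of Group C and 38% of Group B already affected by Day 243, differences in exposure between children can look like waning without any loss of vaccine effect. The interval figures should therefore be labelled descriptive and read with the planned multiple-episode analysis.

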### ***Safety analyses***

Assessment of the safety and reactogenicity of vaccinations will be undertaken by summary listing of all solicited and unsolicited local and systemic adverse events (including results of clinical laboratory investigations where deemed adverse events), considered possibly, probably, or definitely related to vaccination; and line listing of all SAEs.

Safety endpoints will be summarised for Group B and C. The number and percentage of patients in each group who have any local reaction will be compared (using the chi-squared test, and by calculating confidence intervals on differences in percentages). Similarly, the numbers who have any systemic reaction or SAE will be compared between groups. Analysis will also be carried out according to vaccine received.

### ***Immunogenicity Analyses***

Immunogenicity data will be analysed according to a detailed analytical plan.

### ***Exploratory Analysis***

The following analyses will be performed:

- Time to first episode of severe malaria meeting the primary and secondary case definitions of severe malaria over a period of 12 and 24\* months of follow-up after the last vaccination.
- Proportion of participants with an episode of malaria meeting the primary and secondary case definitions of severe malaria, within a period of 12 and 24\* months of follow up after the last vaccination

Analyses for efficacy against severe malaria will be similar to those described previously. These are exploratory analyses that are likely to have low statistical power.

## **10. SAFETY REPORTING**

### Definitions

Definitions for the terms adverse event (or experience), adverse reaction, and unexpected adverse reaction have previously been agreed to by consensus of the more than 30 Collaborating Centres of the WHO International Drug Monitoring Centre (Uppsala, Sweden). Although those definitions can pertain to situations involving clinical investigations, some minor modifications are necessary, especially to accommodate the pre-approval, development environment.

The following definitions, with input from the WHO Collaborative Centre, have been agreed:

#### *Adverse Event*

Any untoward medical occurrence in a clinical investigation subject occurring in any phase of the clinical study whether or not considered related to the vaccine. This includes an exacerbation of pre-existing conditions or events, intercurrent illnesses, or vaccine or drug interaction. Anticipated day-to-day fluctuations of pre-existing conditions, including the disease under study, that do not represent a clinically significant exacerbation will not be considered adverse events. Discrete episodes of chronic conditions occurring during a study period will be reported as adverse events in order to assess changes in frequency or severity.

Adverse events will be documented in terms of a medical diagnosis(es). When this is not possible, the adverse event will be documented in terms of signs and symptoms observed by the investigator at each study visit.

Pre-existing conditions or signs and/or symptoms (including any which are not recognised at study entry but are recognised during the study period) present in a subject prior to the start of the study will be recorded on the Medical History form within the subject's CRF.

#### *Adverse Drug Reaction (ADR)*

An ADR is any untoward or unintended response to a medicinal product. This means that a causal relationship between the study medication and an AE is at least a reasonable possibility, i.e., the relationship cannot be ruled out.

#### *Serious Adverse Event (SAE)*

A serious adverse event (experience) or reaction is any untoward medical occurrence that at any dose:

- results in death,
- is life-threatening,  
**Note:** The term “life-threatening” in the definition of “serious” refers to an event in which the patient was at risk of death at the time of the event; it does not refer to an event which hypothetically might have caused death if it were more severe.
- requires inpatient hospitalisation or prolongation of existing hospitalisation,
- results in persistent or significant disability/incapacity, or
- is a congenital anomaly/birth defect.

Medical and scientific judgment should be exercised in deciding whether expedited reporting is appropriate in other situations, such as important medical events that may not be immediately life-threatening or result in death or hospitalisation but may jeopardise the patient or may require intervention to prevent one of the other outcomes listed in the definition above. These should also usually be considered serious.

#### *Suspected Unexpected Serious Adverse Reactions (SUSARs)*

A SUSAR is a SAE that is unexpected and thought to be related to the investigational product. Administration of further vaccines within the trial will be suspended until a safety review is convened.

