### **Overview of the Safety of ChAd63 ME-TRAP**

Full details of the safety evaluation of ChAd63 ME-TRAP are provided in the Investigator's Brochure. In summary, ChAd63 ME-TRAP has been administered to 309 healthy adults, children and infants in clinical studies in the UK and Africa, generally as the priming vaccination prior to MVA ME-TRAP. All recipients of ChAd63 ME-TRAP have been healthy volunteers participating in clinical trials which have evaluated the safety of vaccination. ChAd63 ME-TRAP has an excellent safety record. Vaccine related adverse events are generally mild in grade, and resolve completely. There have been no vaccine related serious adverse events or SUSARs. Vaccination may provoke a mild local inflammatory reaction. This may include pain, warmth, redness and swelling. Moderate or severe local reactions are unlikely. The intramuscular route is associated with reduced local reactogenicity. Common systemic adverse events resulting from ChAd63 ME-TRAP include headache, feverishness, fatigue and malaise. Volunteers may report a transient

mild 'flu-like illness within 24-48 hours of vaccination which resolves rapidly. Moderate or severe adverse events are unlikely.

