### ***Overview of the Safety of MVA ME-TRAP***

Full details of the safety evaluation of MVA ME-TRAP are provided in the Investigator's Brochure. In summary, MVA ME-TRAP has been administered in phase I and II trials in the UK, The Gambia and Kenya and has been shown to be safe and immunogenic. 772 adults, children and infants in the UK and Africa have received MVA ME-TRAP. Volunteers have received one to three doses of MVA ME-TRAP intra-dermally or intramuscularly at doses of  $3 \times 10^7$  –  $2 \times 10^8$  pfu alone or as part of heterologous prime boost regimes incorporating DNA ME-TRAP, FP9 ME-TRAP and most recently ChAd63 ME-TRAP. Vaccination with MVA ME-TRAP has been well tolerated by all vaccinees to date and the majority of adverse events have been mild in nature. The frequency and intensity of adverse events increases with the dose of MVA ME-TRAP. There have been no vaccine-related SAEs or SUSARs. With intramuscular administration of MVA ME-TRAP, the majority of volunteers experience one or more local adverse event/s such as local pain, warmth and swelling. Local adverse events are generally mild or moderate in grade. Systemic side effects can occur with MVA ME-TRAP and appear to be dose related with symptoms occurring at a higher frequency and greater intensity in volunteers receiving higher doses. Most commonly reported are the sensation of feverishness, malaise, arthralgia, myalgia, headache and nausea or vomiting. Systemic adverse events are generally mild in grade.

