### ***Study duration and timeline***

Proposed timeline for the study:

| Date                   | Activity                                              |
|-------------------------------|--------------------------------------------------------------|
| October 2012                  | Commencement of Recruitment                                  |
| December 2012                 | First vaccination of Group A participants                    |
| January- February 2013        | Second vaccination of Group A participants                   |
| March-April 2013              | First vaccination of Group B and C participants              |
| May 2013                      | Second vaccination of Group B and Group C participants       |
| May/June 2013 – December 2013 | Collection of endpoints for the primary analysis of efficacy |
| To May 2015                   | Efficacy*, safety, and immunogenicity follow-up              |

Depending on whether significant efficacy is seen, and the potential of the vaccines for licensure, we may consider extending the follow up further for pharmacovigilance purposes. In such a case, informed consent will be obtained from study participants.

\* Depending on the outcome of the efficacy analysis of the 12 month data (to June 2014), this may be extended to 24 months following completion of vaccination.

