## **Allocation of participants to Study Group and order of enrolment of Study Groups**

Participants are considered enrolled into the study when they have received the first study vaccination.

The study will commence with the Phase 1 lead-in Safety Evaluation. Thirty eligible participants will be identified as above, and allocated to Group A. The participants will be the following ages at enrolment:

- 5 to 8 months: 10 participants
- 9 to 12 months: 10 participants
- 13 to 17 months: 10 participants

For the Phase 2 Trial, 700 eligible participants will be identified as above, and randomised to Group B or C by an independent statistician, who is not one of the investigators. The randomisation will be stratified according to the following age categories, with varying block sizes:

- Participants aged 5-8 months at enrolment
- Participants aged 9-12 months at enrolment
- Participants aged 13-17 months at enrolment

A randomisation list will be generated and sequentially numbered opaque sealed envelopes will be made for the investigators to ensure treatment concealment. The investigators will not be aware of the randomisation result in the envelopes. The randomisation list, which will be password protected, will be kept in confidence until the final primary analysis is being conducted. As described in Section 7, all investigators will be blinded to allocation of participants in the Phase 2b trial to Group B vs Group C, except the staff responsible for the storage and preparation of the study vaccines.

The interim safety data to Day 21 of trial participation of Group A participants will be presented to the DSMB. DSMB review and approval will be required to administer the first vaccination to Group B and C participants.

The interim safety data to Day 63 of trial participation of Group A participants will be presented to the DSMB. DSMB review and approval will be required to administer the second vaccination to Group B and C participants.

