### **Study termination**

The study will be discontinued in the event of any of the following:

- New scientific information is published to indicate that volunteers in the study are being exposed to undue risks as a result of administration of the IMPs by any route of administration, or as a result of the follow-up schedule.
- Serious concerns about the safety of the IMPs arise as a result of one or more vaccine related SAE occurring in the subjects enrolled in this or any other ongoing study of the IMPs.
- For any other reason at the discretion of the Principal Investigator.

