#### Reporting of Adverse Events

Every SAE occurring throughout the trial must be reported by telephone, email or fax to the sponsor, LSM and DSMB by the investigator as soon as (s)he is alerted of it and within one working day, even if the investigator considers that the adverse event is not related to vaccination. The investigator will then complete a SAE report form as soon as possible and within five working days or seven calendar days.

Any relevant information concerning the adverse event that becomes available after the SAE report form has been sent (outcome, precise description of medical history, results of the investigation, copy of hospitalisation report, etc.) will be forwarded to the Sponsor in a timely manner. The anonymity of the subjects shall be respected when forwarding this information.

SAEs that are suspected to be related to the vaccine will be reported to the Ethics Committee within 15 calendar days of the site becoming aware of the event. If the event is fatal or life-threatening, the event will be reported within 7 calendar days.

Suspected unexpected serious adverse reactions (SUSARs) will be reported according to national regulatory guidelines. The sponsor pledges to inform the Authorities of any trial discontinuation and specify the reason for discontinuation.

The causal relationship between the AE and the product will be evaluated by the investigator. This interpretation will be based on the type of event, the relationship of the event to the time of vaccine administration, and the known biology of vaccine therapy. The following are guidelines for assessing the causal relationship:

No relationship:

No temporal relationship to study product; and

Alternate aetiology (clinical state, environmental or other interventions); and

Does not follow known pattern of response to study product

Unlikely relationship

Unlikely temporal relationship to study product; and

Alternate aetiology likely (clinical state, environmental or other interventions); and

Does not follow known typical or plausible pattern of response to study product

Possible relationship:

Reasonable temporal relationship to study product; or

Event not readily produced by clinical state, environmental or other interventions; or

Similar pattern of response to that seen with other vaccines

Probable relationship:

Reasonable temporal relationship to study product; and

Event not readily produced by clinical state, environment, or other interventions or

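### The pause in vaccination after a SUSAR ends when a safety review is convened; the protocol does not require the review to conclude or to authorise restart

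*Protocol*

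**What the plan says.** Section 10 of the Protocol defines a SUSAR and then gives the dosing rule in one sentence: "Administration of further vaccines within the trial will be suspended until a safety review is convened".

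Section 8 (Allocation of participants to Study Group and order of enrolment of Study Groups) sets two progression gates. The first uses Group A safety data to Day 21 and needs DSMB approval before Groups B and C receive their first dose. For the second gate, "The interim safety data to Day 63 of trial participation of Group A participants will be presented to the DSMB", and then "DSMB review and approval will be required to administer the second vaccination to Group B and C participants". The Lead-in Safety Evaluation paragraph in section 5 repeats that DSMB approvals are needed before Groups B and C are vaccinated.

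On communication, section 10 (Reporting of Adverse Events) says: "Every SAE occurring throughout the trial must be reported by telephone, email or fax to the sponsor, LSM and DSMB by the investigator", within one working day and whether or not the event is thought to be related.

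**The concern.** A pause in dosing protects children only if it lasts until someone has judged whether dosing is safe to continue. To convene a review is to call it together, which comes before its finding. A rule that lifts the suspension at that moment permits, on its face, further doses to infants aged 5 to 17 months while the cause of an unexpected, vaccine-attributed serious reaction is still being examined.

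The protocol shows elsewhere how to write a gate that depends on a decision. It did so for moving from the 30-child lead-in to the 700-child trial, but not for the event-triggered pause.

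**Working it through.** No calculation tests this point. It turns on what each provision requires and when it applies, so the relevant provisions are set side by side.

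| Protocol provision | What it requires | Does it govern restart after a SUSAR? |
|---|---|---|
| SUSARs (section 10) | Suspension until a review is convened | Yes, but with no outcome, reviewing body or authoriser stated |
| Allocation and order of enrolment (section 8) | DSMB approval before first doses and before second doses in Groups B and C | No. These are two one-off gates with Group A data as their stated basis. Neither is re-triggered by a later event |
| Reporting of Adverse Events (section 10) | SAE notification to sponsor, LSM and DSMB; SUSARs reported under national guidelines | No. It informs the DSMB but sets no restart condition |
| Blinding (section 5) and Withdrawal criteria (section 6) | Unblinding or withdrawal of individual children, including on DSMB advice | No. These act on single participants |
| Study termination (section 8) | Discontinuation of the whole study | No. It does not say when a temporary pause ends |
| Follow-up of Adverse Events (section 10) | Following events to resolution; reporting after termination | No |

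Only the SUSAR sentence sets a restart condition, and it is met by convening.

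**When the gap opens.** The outcome depends on where a SUSAR falls relative to the gates:

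1. *Before first-dose approval for Groups B and C.* The DSMB can withhold approval, so there is no gap for these groups.
2. *After first-dose approval and before second-dose approval.* Second doses can be withheld. First doses still due in other children depend on the SUSAR sentence alone.
3. *After both approvals, with doses outstanding.* All remaining doses depend on the SUSAR sentence alone.

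**Whether the third case is realistic on the planned calendar.** Study duration and timeline (section 5) puts first Group A doses in December 2012. Nominal Day 63 for Group A then runs from 1 December 2012 + 63 days = 2 February 2013 to 31 December 2012 + 63 days = 4 March 2013. The entry "First vaccination of Group B and C participants" is dated March-April 2013, with second doses in May 2013. The Group A data named for both gates would therefore be almost all collected before Group B and C dosing begins, and both approvals could be in place while most Group B and C doses are still to be given. This shows only that the case can arise. It does not measure how likely it is or how many doses would be involved.

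**The case against.** The strongest reply is that the point rests on one verb. A pause that lasts until a review is called has little purpose unless the review decides, and no passage suggests that the authors meant dosing to restart first. The interval between convening and deciding is not stated and may be nil. This reply stands as to intent, and it is why the severity is low. It does not change what the sentence permits.

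The second reply is that other safeguards limit the literal reading. The DSMB hears of every SAE within one working day. It can withhold an approval not yet given, and nothing confines it to Group A data when it does so. The Study termination rule is mandatory once "Serious concerns about the safety of the IMPs arise as a result of one or more vaccine related SAE", and one event can suffice. These limit the exposure, but none ties restart to the outcome of a review. The termination trigger is itself a judgement that the review would have to inform.

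Third, the event is rare. For ChAd63 ME-TRAP, given to 309 recipients, the protocol says: "There have been no vaccine related serious adverse events or SUSARs". For MVA ME-TRAP, given to 772, it says: "There have been no vaccine-related SAEs or SUSARs". That is accepted, although both totals pool adults, children and infants.

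Fourth, the gates for Groups B and C are major stage decisions, and an event-triggered pause need not share their wording. That is fair. The two provisions do not contradict each other. The comparison shows only that a decision-based form was available.

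Fifth, the Key Roles section listed in the contents is not in the text available here and may describe the DSMB's remit. The missing name of a reviewing body therefore carries little weight alone. The point rests on the release condition in the sentence itself.

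**Conclusion.** The point holds as a low-severity correction to a safety rule. As written, suspension after a SUSAR ends on convening a review, and no visible provision makes restart depend on the review's conclusion. The consequence needs four things together: a SUSAR, after the relevant DSMB approval, with doses still due, and staff acting on the letter of the rule before the review reports. No risk size and no number of affected doses can be derived from the document. The estimand, power and endpoint definitions are untouched.

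Two stronger readings should be resisted:

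- A reader might infer that the protocol intends dosing to resume during an open review. Nothing in it says so, and the opposite intent is more likely.
- A reader might infer that the Study termination rule would end safety surveillance of children already vaccinated. That rule does not say visits cease. Collection of Adverse Events keeps SAE collection going throughout the study period, and Follow-up of Adverse Events follows existing events and expects possibly related SAEs to be reported even after termination.

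**What to change.** In section 10, under SUSARs, replace the release condition so that administration of further study vaccine is suspended *until the DSMB has reviewed the event and recommended in writing that vaccination may resume*.

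The drafting cost is one sentence. The DSMB is already constituted and already receives every SAE, so no new body or reporting line is needed.

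There is a small operational cost if the decision takes time:

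- **Second doses.** The Day 56 visit has a window of ±14 days, so the latest in-window dose is at Day 56 + 14 = Day 70. For a child due on Day 56, a pause of more than 14 days puts the dose out of window. That child then leaves the According-to-Protocol population (section 9), which requires both vaccines within window and which is the basis of the primary efficacy analysis. The intention-to-treat analysis would still include the child.
- **First doses.** If more than 30 days pass after screening, the Day 0 rules in section 8 require a repeat screening visit.

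Any genuine pause carries these costs. The amendment adds only the time between convening the review and receiving its recommendation.
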